## Abstract

**Background::**

Abdominal obesity occurs when excessive visceral and subcutaneous fat is built up around the abdomen and stomach, which negatively impacts human health. Moxibustion, arose from Traditional Chinese Medicine (TCM), has been widely applied in the treatment of abdominal obesity. Several studies have shown the positive effects of moxibustion in prevention and treatment of endocrine issues and excess body weight. In this context, our study aims to examine the safety and efficacy of the combination of moxibustion and characteristic lifestyle intervention of TCM in the treatment of abdominal obesity.

**Methods/design::**

This study will be a multicenter, randomized, controlled trial conducted from September 2020 to January 2022 that includes 150 participants who have abdominal obesity and meet the eligibility criteria. The participants will be randomly divided into 3 groups in a 2:2:1 allocation ratio. The intervention group will receive moxibustion combined with characteristic lifestyle intervention of TCM; the other group will receive moxibustion combined with lifestyle intervention; the control group will receive lifestyle intervention only. Eight-week moxibustion sessions will be provided to participants assigned to the 2 intervention groups. The characteristic lifestyle intervention of TCM will also last 8 weeks, whereas the lifestyle intervention will last 12 weeks including 8-week treatment period, 4-week follow-up period. The primary outcome is the waist circumference measured by a tape measure. The secondary outcomes include obesity-related indicators, serum biochemical indexs, blood pressure, conversion score of physical symptoms, and measurement of the scale. Adverse events will be recorded during the treatment and follow-up period.

**Discussion::**

The results are expected to provide clinical evidence for the application of the combination of moxibustion and characteristic lifestyle intervention of TCM in patients with abdominal obesity.

**Trial registration::**

ClinicalTrials.gov, NCT04501198, Registered on 9 June 2020.

## Introduction

1

Obesity is a growing global health concern representing an enormous economic and health burden.^[1]^ Excess fat accumulation in the body has shown to be an important risk factor for obesity which can contribute to serious health problems, such as cardiovascular disease, type 2 diabetes mellitus (T2DM), neurodegenerative diseases, liver disease, and even cancer, in particular Alzheimer disease.^[2–4]^ Approximately 650 million people are affected by obesity globally, and this number is estimated to rise in the future.^[5]^ In Iran, the age-adjusted prevalence of overweight or obesity is predicted to be 57.0% in women and 42.8% in men.^[6]^ Moreover, previous studies have confirmed a close association between obesity and psychological problems like anxiety, depression, or stress.^[7]^ It has been shown that nonabdominal obesity was associated with a relatively low risk for mortality and cardiovascular disease, whereas abdominal obesity had higher adverse effects overall, and nonabdominal obesity sometimes even elicited protective effects.^[8]^ In this context, abdominal obesity was a better biomarker to predict mortality than nonabdominal obesity.^[9]^

Nowadays, major clinical treatments of abdominal obesity mainly focus on lifestyle changes (exercise, diet control), drug therapy, surgical treatment, Traditional Chinese Medicine (TCM) intervention, cognition education, among others. The interventions such as diet, physical activity, and cognition education have shown short-term weight loss effects, but poor long-term results and adherence rates.^[10–12]^ In addition, drug therapy is always difficult to be accepted by the majority of obese patients based on its safety. Recent research reported that the surgical treatment of gastrointestinal surgery is the fastest way to lose weight in clinical practice.^[13,14]^ However, only approximately 61.7% population reached the therapeutic goal of weight loss for that the cost and risk of postoperative complications are both high, and there are strict indications, which was unsatisfactory.^[15]^ Therefore, alternative treatment modalities for abdominal obesity are in high demand.

Moxibustion, arose from TCM, has been widely applied in clinical practice. A number of studies have demonstrated that moxibustion is effective in enhancing the immune system, and modifying neurotransmitter levels of central nervous system through repeated acupoint stimulation.^[16,17]^ Studies have shown that moxibustion induces a smoother flow of qi and blood in the human body by using moxa to warm acupoints and body regions, accelerates the blood circulation overall, thereby achieving the effects of disease prevention and health care.^[18]^ Moxibustion can be applied to patients indirectly (placing a medium between the skin and the burning moxa) or directly (placing burn cones directly onto the skin). Moxibustion may be a good choice with patients and doctors for its unique advantages of effectiveness, convenience, and simplicity.

Thus far, moxibustion interventions have been studied in both clinical trials and animal models. Several studies in animal models have shown the positive effects of moxibustion in prevention and treatment of endocrine issues and excess body weight. For example, some researches have proved that moxibustion had beneficial effects on blood lipids, fat accumulation, and decrease of adrenocorticotrophic hormone which plays a key role in decreasing blood flow into fat tissue in rats.^[19,20]^ In one previous clinical trial, Mestre et al found that obesity index decreased and the rate of body weight gain was slowed after the moxibustion treatment.^[21]^ Another study conducted by Huang et al^[22]^ showed that moxibustion was effective in reducing blood lipid indexes and the levels of Leptin, Resistin for the patients with obesity complicated with hyperlipidemia. All of these results suggest that moxibustion has beneficial effects on both body weight management and blood lipids.

To evaluate the exact effect of moxibustion on the clinical efficacy of abdominal obesity, we will conduct a 3three-arm parallel clinical trial. In this study, we will try to combine the advantages of moxibustion and characteristic lifestyle intervention of TCM in the treatment of abdominal obesity. To achieve this, a standardized multicenter, randomized, controlled trial will be carried out to improve the treatment protocol and evaluation criteria, which can provide an objective theoretical basis and methodology for the treatment of abdominal obesity by moxibustion combined with characteristic lifestyle intervention of TCM.

## Methods/design

2

### Ethics approval

2.1

This study was approved by the Ethics Committee of Hubei Provincial Hospital of TCM, HBZY2020-C36–01. The recruitment did not start at other centers in this trial until the local ethical approval had been obtained. This study is registered at https://register.clinicaltrials.gov/prs/app/action/LoginUser?ts=1&cx=-jg9qo4(NCT04501198). Written informed consents will be provided by all participants before they were enrolled in this study. Their personal information will be collected, and maintained in an independent closet to protect confidentiality before, during, and after the clinical trial.

### Study design

2.2

This randomized controlled trial will be conducted at the Department of Acupuncture of five hospitals including Hubei Provincial Hospital of Traditional Chinese Medicine, Shanxi Provincial Hospital of Traditional Chinese Medicine, Shenzhen Bao’an Traditional Chinese Medicine Hospital Group, Wuhan Hospital of Traditional Chinese and Western Medicine, Xiangyang Hospital of Traditional Chinese Medicine from September 2020 to January 2022. The participants recruited from our outpatient departments will be randomly allocated to three groups, these are the intervention group (moxibustion combined with characteristic lifestyle intervention of TCM, n = 60,expected); the other intervention group (moxibustion combined with lifestyle intervention, n = 60,expected) or the control group (lifestyle intervention, n = 30, expected). The participants in the 2two intervention groups will receive 48 sessions of moxibustion treatment over 8 weeks. The characteristic lifestyle intervention of TCM will also last 8 weeks, whereas the lifestyle intervention will last 12 weeks including 8-week treatment period, 4-week follow-up period. The study design is depicted in Figure 1.

**Figure 1 F1:**
[figure not shown]
Flowchart of the trial.

### Participants

2.3

#### Diagnostic criteria

2.3.1

According to the criteria in the Comprehensive Medical Management Guidelines for Obese People jointly issued by the American Society of Clinical Endocrinologists (AACE) and the American College of Endocrinology (ACE) in May 2016:^[23]^ waist circumference (WC) ≥85 cm for male and 80 cm for female can be diagnosed as abdominal obesity.

#### Inclusion criteria

2.3.2

The inclusion criteria for the participants are as follows:

Satisfying the criteria for the diagnosis of abdominal obesity;18 years’ old≤age≤55 years’ old;Being able to fully understand and voluntarily sign informed consent.

#### Exclusion criteria

2.3.3

The exclusion criteria for the participants consist of:

Presence of endocrine disorders such as: polycystic ovary syndrome; Cushing syndrome; uncorrected thyroid disease.Presence of diabetes mellitus, or hypertension, or abnormal liver and kidney functions, or mental diseases.Pregnant or lactating state, women who plan to become pregnant within 12 weeks.History of bulimia, anorexia, or any other eating disorders.Use of medications in the past 3 months, such as diet drugs, corticosteroids, antidepressants, which may affect weight or appetite.History of surgical weight loss, postoperative adhesions.History of participating in a clinical study of weight loss or any other therapies to lose weight in the past 3 months.Presence of local skin rupture, allergy, and scar constitution.Unable to cooperate with the research caused by other diseases or reasons.

#### Recruitment

2.3.4

All participants will be recruited by clinicians with a medical practitioner qualification certificate in the outpatient clinics of these 5 participating hospitals. Recruitment methods including hospital website, hospital Public Accounts, and local advertising which will be put up on campus or communities.

#### Patient safety

2.3.5

Potential adverse events associated with moxibustion included rash, skin allergy, and infection. They will be recorded by the acupuncturist clinicians when any adverse events occur, and the intervention will be immediately stopped but temporarily. Three experts from different fields from Hubei Provincial Hospital of TCM compose an independent Safety Monitoring Board, who has the right to make the final decision to terminate the study. All these experts will monitor the safety and performance of this trial to make sure that the study goes smoothly.

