### Intervention

2.4

After baseline measurements, patients satisfying the inclusion criteria will be randomly divided into 1 of the 3 treatment groups, as shown below:

1.Group A: Lifestyle intervention.2.Group B: Moxibustion combined with lifestyle intervention.3.Group C: Moxibustion combined with characteristic lifestyle intervention of TCM.

All the participants will be instructed to return to visit the doctor every 2 week.

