##### Moxibustion

2.4.2.1

The moxibustion acupoints will be selected as ①*zhongwan, guanyuan, shenque,* and *zusanli*; ②*pishu,shenshu.* The location of the acupoints was based on the national GB-12346-90 acupoints standard.^[25]^ Acupoints group ① will be selected on Monday, Wednesday, and Friday, Acupoints group ② will be selected on Tuesday, Thursday, Saturday. The lit moxa (moxa cone of 1.5 cm in diameter, planted in Nanyang, China) was placed 2 to 3 cm above the skin, and the surface temperature of the local skin will be maintained at 45°C ± 2 °C for 20 minutes. Moxibustion treatment will be applied once every day, 6 times per week, for 8 consecutive weeks. The treatment will be delayed during the menstrual period.

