##### Moxibustion

2.4.3.1

The specific methods and intervention time in this group will be the same as that for the group B.

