#### Primary outcome measures

2.5.1

WC will be used as the primary outcome measure. This index will be assessed on week 0, 2,4,6, 8, and 12.

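### Adverse events are recorded ad hoc by acupuncturist clinicians while Groups B and C have 44 to 48 more contacts than Group A, so between-arm rates risk unequal ascertainment

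*Protocol article*

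**What the plan says.** The Patient safety section (2.3.5) opens with examples of expected events: "Potential adverse events associated with moxibustion included rash, skin allergy, and infection". It then names the recorder and the timing: "They will be recorded by the acupuncturist clinicians when any adverse events occur". The abstract adds a time window without restricting it to any arm: "Adverse events will be recorded during the treatment and follow-up period".

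Contact with clinicians differs by arm. Study design (2.2) gives the two moxibustion groups "48 sessions of moxibustion treatment over 8 weeks". The Group B moxibustion section (2.4.2.1) gives the frequency: "Moxibustion treatment will be applied once every day, 6 times per week, for 8 consecutive weeks". For Group C (2.4.3.1), "The specific methods and intervention time in this group will be the same as that for the group B". Group A has lifestyle intervention only. The contact shared by all arms is set in the Intervention section (2.4): "All the participants will be instructed to return to visit the doctor every 2 week". Waist circumference follows a similar timetable (2.5.1): "This index will be assessed on week 0, 2,4,6, 8, and 12".

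Safety is named as an aim in the abstract and twice in the Discussion. Section 2.8 blinds the researchers who evaluate the outcomes. The Discussion accepts that the moxibustion therapist cannot be fully blinded and that this carries a risk of bias.

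**The concern.** When events are recorded as they come up, the chance that an event reaches the record depends on how often the participant meets the person recording. Here that frequency is set by the randomised arm. A short-lived rash, a minor infection or a spell of dizziness in Group B or C can be mentioned at a session within a day or two. The same event in Group A may have to be remembered for up to two weeks, and the article does not say that anyone asks about it. The recorder who gives moxibustion also knows that the participant is not in Group A.

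At stake is the reading of the safety results. A trial with a safety aim and a lifestyle-only arm will be read by comparing event rates across arms. An excess in B and C could come from treatment, from recording, or from both, and the analysis could not separate them afterwards, because events never asked about in Group A cannot be reliably recovered.

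The issue concerns events that any arm can have. Local reactions to moxibustion cannot occur in Group A, so they are not under-recorded there.

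**Working it through.** **Inputs.** Session frequency and duration: section 2.4.2.1, extended to Group C by 2.4.3.1. Stated session total: section 2.2. Two-weekly visits in all arms: section 2.4. Assessment weeks: section 2.5.1. Capture probabilities: not in the article, so assumed below.

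**Step 1: reproduce the stated figure.** 6 sessions per week × 8 weeks = 48 sessions, which matches section 2.2.

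**Step 2: count post-baseline contacts per participant.** The article does not say whether the two-weekly visits fall on session days, nor whether they continue two-weekly after week 8. Both choices are shown. If separate, B/C contacts = visits + 48. If the four treatment-period visits (weeks 2, 4, 6, 8) fall on session days, B/C contacts = visits + 44.

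| Visits counted | A | B/C, separate days | Ratio | B/C, same days | Ratio |
|---|---|---|---|---|---|
| Weeks 2, 4, 6, 8 | 4 | 52 | 13.0 | 48 | 12.0 |
| Weeks 2, 4, 6, 8, 12 | 5 | 53 | 10.6 | 49 | 9.8 |
| Two-weekly to week 12 | 6 | 54 | 9.0 | 50 | 8.3 |

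The excess over Group A is 44 to 48 contacts, all within the 8 treatment weeks. The ratio is 12 to 13 in the treatment period and runs down to about 8 once follow-up visits are counted. B and C have the same number of sessions, so the imbalance affects comparisons with A, not B against C.

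**Step 3: what unequal capture could do.** Let true incidence p be equal in all arms, and let c be the share of events captured. Observed incidence = p × c, so the spurious risk ratio = c(B/C) ÷ c(A), and p cancels. With c(B/C) assumed to be 0.95:

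- c(A) = 0.90: 0.95 / 0.90 = 1.06
- c(A) = 0.70: 0.95 / 0.70 = 1.36
- c(A) = 0.50: 0.95 / 0.50 = 1.9
- c(A) = c(B/C): ratio 1.0, no distortion

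At an assumed true incidence of 10%, the first three cases would show 9.5% in B and C against 9%, 7% and 5% in A.

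These values show a range; they are not an estimate. A 13-fold difference in contacts does not mean a 13-fold difference in capture, since one well-put question at a two-weekly visit can recover most events of the past fortnight.

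**The case against.** The strongest reply has several parts.

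- **The abstract's statement covers all arms.** It promises recording through treatment and follow-up. Moxibustion ends at week 8, so recording in follow-up cannot depend on the sessions. This stands: Group A is not left without any recording.
- **The recorder is not said to be the treating therapist.** The trial runs in Departments of Acupuncture, so the doctor who sees Group A every two weeks may also be an acupuncturist clinician. This stands too, but it does not remove the difference in contact frequency or supply a common enquiry.
- **An article condenses the protocol.** Adverse event forms may sit in the full protocol, and the schedule table is not reproduced here. The absence of a form is therefore no finding. The point rests on the recording rule that the article does state, which, followed as written, ties capture to arm.
- **No between-arm test of adverse events is described.** Correct. The risk arises as soon as rates are set side by side, which the safety aim and the lifestyle-only arm invite.
- **Therapist blinding is already listed as a limitation.** True, but in general terms, without a link to adverse event recording.

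A reader might also infer that burns, or events from the decoction, diet or exercise, are excluded from recording. The text does not support that: the three named events are examples of potential events, not a closed list.

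**Conclusion.** The point holds as a risk. As written, adverse event recording is ad hoc, is assigned to acupuncturist clinicians, and operates across arms that differ by 44 to 48 clinician contacts per participant (about 8 to 13 times as many in B and C). Adverse event rates compared with Group A are therefore open to differential ascertainment.

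It is tempting to go further and say that the safety comparison is biased, or that Group A will look artificially clean. The article does not support that. It gives no event rates or capture rates, and it does not say what is asked at the two-weekly visits. If those visits capture events as fully as the sessions do, the distortion is zero. The spurious risk ratios of 1.06 to 1.9 rest wholly on the assumed capture of 95% against 90% to 50%. The figure of 48 extra contacts is likewise an upper end, reached only if no visit falls on a session day.

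No sample size, power or significance level is affected. A change is worth making because safety is a stated aim and the remedy is cheap, but it has to be in place while data are being collected.

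**What to change.** At each existing two-weekly visit and at week 12, put the same adverse event enquiry to all three arms, worded to cover events from any study component (moxibustion, decoction, exercise, diet), and record the answers on the CRF. Base any between-arm comparison, such as participants with at least one event, on these common visits only. List events noted at moxibustion sessions separately as local treatment reactions, without comparing them with Group A.

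The cost is one more CRF page at visits that already take place; no visits are added. There is one small downside. The visits coincide with the waist measurement by blinded evaluators, and answers about skin reactions could reveal the arm. The enquiry should therefore come after the waist measurement or be made by someone other than the blinded assessor.

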### Intervention

2.4

After baseline measurements, patients satisfying the inclusion criteria will be randomly divided into 1 of the 3 treatment groups, as shown below:

1.Group A: Lifestyle intervention.2.Group B: Moxibustion combined with lifestyle intervention.3.Group C: Moxibustion combined with characteristic lifestyle intervention of TCM.

All the participants will be instructed to return to visit the doctor every 2 week.

#### Group A (lifestyle intervention)

2.4.1

The following living habits are recommended:^[24]^

All participants who weigh 113.6kg (250 lb.) will be prescribed a diet of 1200 to 1499 kcal/day, which comprise of conventional foods with approximately 20% to 35% from fat, 15% to 20% kcal from protein, and the remainder from carbohydrate. Whereas for those who weighed≥113.6 kg, a diet of 1500 to 1800 kcal/day will be prescribed. Meanwhile, all participants will be instructed to record their food and calorie intake daily, and low-to-moderate intensity physical activities such as jogging and walking will be instructed to them for at least 5 days per week continually, and for at least 210 min/week, preferably ≥270 min/week.

All patients will be instructed to keep a diet and exercise diary.

The intervention time of lifestyle intervention includes the treatment period of 8 weeks and the follow-up period of 4 weeks.

#### Group B (Moxibustion combined with lifestyle intervention)

2.4.2

##### Moxibustion

2.4.2.1

The moxibustion acupoints will be selected as ①*zhongwan, guanyuan, shenque,* and *zusanli*; ②*pishu,shenshu.* The location of the acupoints was based on the national GB-12346-90 acupoints standard.^[25]^ Acupoints group ① will be selected on Monday, Wednesday, and Friday, Acupoints group ② will be selected on Tuesday, Thursday, Saturday. The lit moxa (moxa cone of 1.5 cm in diameter, planted in Nanyang, China) was placed 2 to 3 cm above the skin, and the surface temperature of the local skin will be maintained at 45°C ± 2 °C for 20 minutes. Moxibustion treatment will be applied once every day, 6 times per week, for 8 consecutive weeks. The treatment will be delayed during the menstrual period.

##### Lifestyle intervention

2.4.2.2

The lifestyle intervention in this group will be the same as that for the group A.

#### Group C (Moxibustion combined with characteristic lifestyle intervention of TCM)

2.4.3

##### Moxibustion

2.4.3.1

The specific methods and intervention time in this group will be the same as that for the group B.

##### Characteristic lifestyle intervention of TCM

2.4.3.2

In this study, xiusheng decoction, traditional exercises, and modern lifestyle intervention will be combined as the characteristic lifestyle intervention method of TCM to help participants establish healthy living habits.

(1)Xiusheng DecoctionThe package (specification: 6 g) manufactured by hubei ji’antang pharmaceutical Co., Ltd. is adopted, the manufacturer conforms to GMP standard with strict quality control. The components of this product are all Chinese medicines with medicinal and food homologous (composition: coix seed, black tea, tuckahoe, lotus leaf, xylitol, dextrin), and the dosage form is granule. Each decoction should be taken twice a day, orally half an hour after meals. The treatment will be delayed during the menstrual period. The course of intervention will last for 8 weeks.(2)Traditional exercisesIt is recommended that the “fitness qigong • ba duan jin” issued by the fitness qigong management center of general administration of sport of China be taken as the standard for performing meritorious exercises. A full set of fitness qigong consists of 8 forms in which the essentials of these movements refer to “Chinese Traditional Health sports and Health Preservation,” and the movements will be instructed by the extension agents of traditional sports who have been trained by Shanghai qigong research institute. The exercise will be taken for 35∼40 minutes every day, 7 times a week. The intervention will be conducted for 8 weeks.(3)Modern lifestyle interventionThe lifestyle intervention in this group will be the same as that for the group A.

